#### **4.3 Restrictions during the study**

- Patients will be abstinent from alcohol throughout the study.
- Smoking will be restricted (< 10 cigarettes/day) during the study and will be prohibited 1 hour before vital signs and ECG assessments.
- The patient donated blood during the study and 8 days after the end of medication;
- Males or females of childbearing potential are required to use 8 g of contraception during the study.

#### **4.4 Patient Discontinuation/Withdrawal**

##### **4.4.1 Treatment discontinuation**

##### **1) Liver enzyme and other laboratory tests**

In any case, discontinuation of study drug should be considered after joint discussion of investigator and the sponsor;

When a patient has baseline ALT/AST < 1.5 × ULN:

- ALT or AST ≥ 5 × ULN

- ALT or AST  $\geq 4$ x ULN for more than 2 weeks
- ALT or AST  $\geq 3$ x ULN and TBL  $> 2$ x ULN or international normalized ratio (INR)  $\geq 1.5$
- ALT or AST  $\geq 3$ x ULN with symptoms of fatigue, nausea, vomiting, right upper quadrant pain/tenderness, fever, rash and/or eosinophilia ( $> 5\%$ )
- ALP  $> 3$ x ULN
- ALP  $\geq 2.5$  x ULN and TBL  $> 2$  x ULN
- ALP  $\geq 2.5$ x ULN with symptoms of fatigue, nausea, vomiting, right upper quadrant pain/tenderness, fever, rash and/or eosinophilia ( $> 5\%$ )

When a patient has baseline ALT/AST  $\geq 1.5$  x and  $< 2$  x ULN:

- ALT or AST  $\geq 4$  x baseline
- ALT or AST  $\geq 3$  x baseline for more than 2 weeks
- ALT or AST  $\geq 2$  x baseline and TBL  $> 2$  x ULN or international normalized ratio (INR)  $\geq 1.5$
- ALT or AST  $\geq 2$  x baseline with symptoms of fatigue, nausea, vomiting, right upper quadrant pain/tenderness, fever, rash, and/or eosinophilia ( $> 5\%$ )

Note: If the patient is found to have ALT/AST at screening, the baseline data will be collected at least 2 weeks apart.

- CK elevation  $> 5$ x ULN
  - Lipase and/or amylase  $\geq 3$  x ULN, the possibility of pancreatitis should be considered by the investigator (Table 5)
- 2) Hyperglycemia/hypoglycemia:
- The study drug should be discontinued due to deterioration in blood glucose control during the trial, fasting blood glucose  $> 13.3$  mmol/L with other excluded causes (e.g., increased blood glucose due to concurrent disease);
- The patient had a severe hypoglycemic event or persistent hypoglycemia (see section 8.3.4 for details);
- 3) The patient was inadvertently withdrawn from the study if the sponsor or investigator determined that the patient did not meet the enrollment criteria.
- #### 4.4.2 Withdrawal
- 1) Participation in other clinical trials during the trial is defined as signing the informed consent form for other trials;

- 2) The investigator may terminate or withdraw a subject from the study because of AEs. (Considering that gastrointestinal adverse reactions may be related to the efficacy, it is recommended that the investigator may consider to adjust the titration rate at first. Only if the severe adverse events continues after adjustment, the investigator will terminate the patient because of intolerance);
- 3) Patients with poor compliance who do not receive medication or test before completing the whole trial and cannot insist on completing the trial as planned, including patients who cannot do a good job in diet control, do not take medicine as required, or have other conditions that may affect the efficacy evaluation;
- 4) Withdrawal of consent by the patient;
- 5) Patients with blindness due to various reasons;
- 6) Female patient becomes pregnant;
- 7) The investigator considers it inappropriate to continue to participate in the trial.

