  - Blood biochemistry: aspartate aminotransferase (AST), alanine aminotransferase (ALT), total bilirubin (TBIL), direct bilirubin (DBIL), albumin (ALB), total protein, glutamyl transpeptidase (GGT), alkaline phosphatase (ALP), lactate dehydrogenase (LDH), serum potassium, serum sodium, serum calcium, serum chloride, uric acid (UA), urea, creatinine (Cr);

- 3) Blood lipids: total cholesterol (TC), triglyceride (TG), high-density lipoprotein cholesterol (HDL-C), low-density lipoprotein cholesterol (LDL-C);
- 4) Coagulation function: prothrombin time (PT), activated partial thromboplastin time (APTT), international normalized ratio (INR);
- 5) Urinalysis: urine pH, urine protein, urine glucose, urine red blood cells, urine white blood cells;
- 6) Myocardial enzyme spectrum: creatine kinase (CK), creatine kinase isoenzyme (CK-MB);
- 7) Amylase and lipase;
8. 12-lead electrocardiogram (ECG): For Day (D) 1/D29/D57/D78 visits, ECG should be performed once before administration (P) and at 12 hours  $\pm$  30 minutes after administration, and for other visits, ECG should be performed only once before administration or on the day of visit. Any clinically significant findings from ECGs observed by the investigator may additionally perform ECG per the actual situation.
9. Serum virology: including human immunodeficiency virus (HIV) antibody, hepatitis B (5 items), hepatitis C (HCV) antibody and syphilis antibody.
10. Serum pregnancy test is preferred and urine pregnancy may be substituted if the site is unable to do so.
11. Thyroid function parameters include: thyroid stimulating hormone (TSH), free T3 (FT3) and free T4 (FT4).
12. Eligible patients will be trained in self-monitoring of blood glucose (SMG), and a patient diary card and glucometer will be dispensed.
13. Seven points fingertip capillary blood glucose refers to glucose collected from 7 finger stick at fasting, 2 hours after breakfast ( $\pm$  30 min), before lunch, 2 hours after lunch ( $\pm$  30 min), before dinner, 2 hours after dinner ( $\pm$  30 min), and at bedtime, and the collection date will be completed within 2 days before D-1, D29, D57, and D85 visits. Fasting state will be defined as a 10-hour fast.

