11. Clinically symptomatic liver disease, acute or chronic hepatitis, or transaminases (ALT and AST) and alkaline phosphatase (ALP) > 2 × upper limit of normal and total bilirubin > upper limit of normal at screening.

12. Calcitonin  $\geq 15$  ng/L at screening.
13. EGFR  $< 60$  mL/min/1.73 m^2 at screening, estimated using the modified MDRD formula:  $eGFR = 175 \times [(\text{serum creatinine } (\mu\text{mol/L})/88.4)]^{-1.234} \times [\text{age (years)}]^{-0.179} \times 0.79$  (female) or  $\times 1$  (male).
14. History or presence of psychiatric disorder at screening that would make participation in this study inappropriate at the discretion of the investigator.
15. Have Diagnosed of gastroparesis or received any form of obesity surgical procedure, or had abnormal gastric emptying considered clinically significant by the investigator.
16. Known history of regular drug abuse.
17. Positive human immunodeficiency virus (HIV) antibody and/or HIV infection at screening, or positive syphilis antibody.
18. History of hepatitis B and/or positive hepatitis B surface antigen at screening or positive hepatitis C (HCV) antibody at screening.
19. Previous diagnosis of Gilbert's syndrome.
20. International normalized ratio (INR) of prothrombin time greater than the upper limit of normal at screening.
21. History of medullary thyroid C-cell carcinoma, MEN (multiple endocrine neoplasia) syndrome 2A or 2B, or relevant family history.
22. Diagnosed with autonomic neuropathy, manifested as: urinary retention, resting tachycardia, orthostatic hypotension, and diabetic diarrhea.
23. Significant weight change with a percentage change  $> 5\%$  within 3 months prior to screening.
24. Donation of  $\geq 400$  mL of blood or excessive blood loss or bone marrow transplantation within 3 months before screening, or presence of hemoglobinopathy, hemolytic anemia, sickle cell anemia, or hemoglobin  $< 110$  g/L (men) or  $< 100$  g/L (women).
25. Hyperthyroidism or hypothyroidism confirmed by clinical assessment and/or TSH abnormality that, in the opinion of the investigator, may increase the risk of the patient.
26. Use of antidiabetic drugs other than metformin within 2 months prior to screening.

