### 8.3.3 Hepatic dysfunction events

If abnormal AST and/or ALT levels are complicated by abnormal elevation of total bilirubin levels, drug-induced liver injury will be considered if the following conditions are met and there is no other cause for liver injury. Such situations should always be considered important medical events.

Table 6 Hepatic Impairment to be Reported as an SAE

| Baseline Period  | Normal (AST/ALT and total bilirubin)                                                                                                                                | Abnormal (AST/ALT and total bilirubin)                                                                                                                |
|------------------|---------------------------------------------------------------------------------------------------------------------------------------------------------------------|-------------------------------------------------------------------------------------------------------------------------------------------------------|
| Treatment period | ALT or AST $\geq 3 \times \text{ULN}$
With total bilirubin $\geq 2 \times \text{ULN}$
AND alkaline phosphatase $\leq 2 \times \text{ULN}$
And no hemolysis | AST or ALT $\geq 8 \times \text{ULN}$
With total bilirubin increase $\geq 1 \times \text{ULN}$ or total bilirubin value $\geq 3 \times \text{ULN}$ |

Patients should return to the study site for evaluation as soon as possible (preferably within 48 hours) after acknowledge of the abnormal results. Assessments should include laboratory tests, detailed history and physical assessment. The abnormality should be considered the the relationship to liver tumors (primary or secondary).

In addition to repeating AST and ALT, laboratory tests to be performed include albumin, creatine kinase, total bilirubin, direct and indirect bilirubin,  $\gamma$ -glutamyltransferase, prothrombin time/international normalized ratio, and alkaline phosphatase. Detailed history collection should include: history of drinking, acetaminophen, soft drugs, various supplements, traditional Chinese medicines, history of exposure to chemical drugs, family history, occupational exposure, sexual behavior, travel history, history of exposure to jaundiced patients, surgery, blood transfusion,

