### **Laboratory Abnormalities**

Clinically significant laboratory abnormalities should be reported as AEs. It is the responsibility of the investigator to review all abnormal laboratory findings and make medical judgment as to whether each abnormal laboratory finding should be reported as an AE.

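### The ALP prompts in section 4.4.1 are printed only for patients entering with ALT/AST below 1.5 × ULN, so those entering at 1.5 to below 2 × ULN have no numeric prompt for a cholestatic reaction

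*Combined protocol and SAP*

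**What the plan says.** Under item 1) of protocol section 4.4.1, the liver criteria are prompts and not automatic stops: "discontinuation of study drug should be considered after joint discussion of investigator and the sponsor". Two lists follow, split by baseline transaminases.

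- The first list is headed "When a patient has baseline ALT/AST < 1.5 × ULN" and has seven bullets. Four start from ALT or AST in multiples of ULN. Three start from ALP: above 3 × ULN; at least 2.5 × ULN with total bilirubin (TBL) above 2 × ULN; and at least 2.5 × ULN "with symptoms of fatigue, nausea, vomiting, right upper quadrant pain/tenderness, fever, rash and/or eosinophilia".
- The second list covers baseline ALT/AST from 1.5 to below 2 × ULN and has four bullets. All start from ALT or AST in multiples of baseline (4, 3, 2 and 2). ALP does not appear.

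A note on repeat baseline sampling comes next, then lines on CK and on lipase/amylase that appear to apply to everyone.

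Patients in the second group can be enrolled. Exclusion criterion 11 bars "transaminases (ALT and AST) and alkaline phosphatase (ALP) > 2 × upper limit of normal and total bilirubin > upper limit of normal" at screening, so transaminases between 1.5 and 2 × ULN do not exclude. The only other numeric liver rule is Table 6 in section 8.3.3, which opens with "If abnormal AST and/or ALT levels are complicated by abnormal elevation of total bilirubin levels".

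**The concern.** There is a reason to restate the transaminase limits as multiples of baseline when the baseline transaminases are already raised. That reason does not extend to ALP. The three ALP limits are multiples of ULN and make no use of ALT or AST, and the protocol gives no ground for confining them to patients with the more normal entry values.

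Followed as printed, the same ALP and bilirubin results prompt a sponsor discussion in one patient and not in another, and the second patient is the one who entered with the more abnormal liver tests. Safety and tolerability are the primary endpoint of this trial, and biliary events are not remote. Table S3 records cholecystitis, cholelithiasis and abnormal hepatic function, each in one patient of the 3.0 mg group, with one patient in total in that organ class. That patient's ALP and baseline stratum are not given, so this shows relevance and not that the gap was reached.

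**Working it through.** The plan has no figure to reproduce here. The check applies each rule as printed.

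**Step 1. The bullets (section 4.4.1).**

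| | Baseline < 1.5 × ULN | Baseline 1.5 to < 2 × ULN |
|---|---|---|
| 1 | ALT/AST ≥ 5 × ULN | ALT/AST ≥ 4 × baseline |
| 2 | ALT/AST ≥ 4 × ULN for > 2 weeks | ALT/AST ≥ 3 × baseline for > 2 weeks |
| 3 | ALT/AST ≥ 3 × ULN and TBL > 2 × ULN or INR ≥ 1.5 | ALT/AST ≥ 2 × baseline and TBL > 2 × ULN or INR ≥ 1.5 |
| 4 | ALT/AST ≥ 3 × ULN with symptoms or eosinophilia | ALT/AST ≥ 2 × baseline with symptoms or eosinophilia |
| 5 | ALP > 3 × ULN | none |
| 6 | ALP ≥ 2.5 × ULN and TBL > 2 × ULN | none |
| 7 | ALP ≥ 2.5 × ULN with symptoms or eosinophilia | none |

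In the right-hand column the lowest requirement is 2 × baseline. If the INR condition is tied to the ALT/AST condition in bullet 3, no bullet can be met while ALT/AST stays below 2 × baseline, however high ALP rises.

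**Step 2. Worked cases.** The on-treatment values are assumed for illustration and given in multiples of ULN. ALT is unchanged from baseline and INR is below 1.5.

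| Case | Baseline ALT 1.4 | Baseline ALT 1.6 |
|---|---|---|
| A: ALP 4, TBL 2.5, no symptoms | bullets 5 (4 > 3) and 6 (4 ≥ 2.5, 2.5 > 2): 2 of 7 | ALT is 1.0 × baseline: 0 of 4 |
| A with symptoms | bullets 5, 6 and 7: 3 of 7 | 0 of 4 |
| B: ALP 2.6, TBL 0.8, right upper quadrant pain | bullet 7 (2.6 ≥ 2.5): 1 of 7 | 0 of 4 |

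**Step 3. Where the gap ends.** In the upper group, 2 × baseline runs from 2 × 1.5 = 3.0 × ULN to just under 2 × 2 = 4.0 × ULN. A mixed reaction that reaches this level with bilirubin above 2 × ULN or symptoms does prompt a discussion. With baseline 1.6, ALT 3.2 (3.2 / 1.6 = 2.0 × baseline), TBL 2.5 and no symptoms, bullet 3 is met: 1 of 4.

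**Step 4. Table 6 (section 8.3.3).** The normal-baseline column needs ALT or AST ≥ 3 × ULN and also requires ALP ≤ 2 × ULN, so cases A and B fail both conditions. The abnormal-baseline column needs ALT or AST ≥ 8 × ULN, and case A has 1.6. If that column's last condition, TBL ≥ 3 × ULN, is read as standing alone, case A (2.5) and case B (0.8) still do not meet it.

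**Step 5. Other safety rules.**
- The escalation criteria in section 3.2.3 contain no liver item.
- The list of events of special interest in section 8.3 names raised transaminases and not ALP.
- The remaining routes are item 2 of the intolerance criteria below Table 1, items 2 and 7 of section 4.4.2, severe related events under section 8.3, and the paragraph on laboratory abnormalities in section 8.6.3 ("It is the responsibility of the investigator to review all abnormal laboratory findings and make medical judgment"). All rest on judgement and give no ALP threshold.

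**Step 6. Data available.** ALP and total bilirubin are in the biochemistry panel (notes to Table 2). The schedule places that panel on D15, D29, D57 and D85 and at early termination. Three of these (D15, D29, D57) come before the last dose on D78, when a prompt can still change treatment.

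**The case against.** The strongest objection is that the layout is being read selectively. The ALP lines are confined to the first group because they stand above the second heading, yet the CK and lipase/amylase lines, which stand below that heading, are taken as common to all. The list structure in this part of the text is visibly disturbed, and the ALP lines may have been meant for everyone. That is possible. But no wording makes them common, and if it was the intention, the same edit is needed to say so.

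Two readings would narrow the gap. If INR ≥ 1.5 in bullet 3 stands alone, a patient with raised INR is caught without any ALT change. If TBL ≥ 3 × ULN in Table 6 stands alone, severe cholestasis in a patient with abnormal baseline becomes a reportable serious event. Neither is the natural reading, and neither supplies an ALP prompt. The worked cases have INR below 1.5 and TBL below 3 × ULN, so they do not test these readings at their limits.

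Other routes also operate. Nausea, vomiting and severe related events go to the sponsor within 24 hours as events of special interest, in both groups. Note 2 to Table 5 calls for specialist consultation, stopping dosing and informing the sponsor when the investigator suspects acute pancreatitis, which could cover the pain in case B. The sentence that introduces the lists can be read as inviting a discussion for any patient. Adverse events and laboratory summaries are collected and analysed alike in both groups, so the primary analysis itself is not split by this rule. These points stand, and they reduce the consequence to a missing numeric trigger. Monitoring is not absent.

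Reach is also limited. Only 24 patients (3 × 8) are planned for IBI362, and the gap further needs a marked ALP rise with transaminases below 2 × baseline.

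**Conclusion.** The point holds. Section 4.4.1 prints three ALP prompts for baseline ALT/AST below 1.5 × ULN and none for 1.5 to below 2 × ULN, and no other section gives an ALP threshold that would prompt a discussion. In case A the contrast is 2 of 7 against 0 of 4, and in case B 1 of 7 against 0 of 4.

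This rests on reading the lists as printed, with the INR condition tied to ALT/AST, and it concerns only reactions in which ALT/AST stays below 2 × baseline. The size of the affected group is not stated and may be nil. It should be corrected because it is an unexplained asymmetry in a safety rule and is easily closed. It does not threaten the conduct of the trial.

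**What to change.** Take the three ALP lines out of the first list and put them in a block stated to apply to all patients whatever their baseline ALT/AST, beside the CK and lipase/amylase lines, with wording that makes those lines common too. Leave the two ALT/AST lists unchanged. With this change, case A at baseline 1.6 × ULN meets 2 prompts and case B meets 1, the same ALP prompts as at baseline 1.4.

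The medical team should confirm the ALP limits, in particular for a patient whose ALP is already raised at entry. Exclusion criterion 11 as printed joins its transaminase, ALP and bilirubin limits with a conjunction, so raised ALP alone does not exclude.

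The cost is three lines moved in a protocol amendment, that one medical decision, and a few more discontinuation discussions. No test or visit is added.

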#### 4.4.3 Withdrawal procedures

If the decision is made to permanently discontinue study drug, the patient will be withdrawn from the study and an End of Treatment Visit should be performed. Reasonable efforts should be made to persuade the patient to complete the follow-up visit. These visits are described in Section 6. The date of last dose for study drugs and the reason for withdrawal will be recorded in the eCRF.

### 4.5 Patients Withdrawal

If the patient discontinues study treatment and actively withdraws consent for collection of follow-up data, then no additional data collection should occur; however, patients may elect to withdraw consent for study treatment but continue to accept follow-up to assess safety/efficacy.

## 5. Study Drug and Other Therapies

### 5.1 Treatment Allocation

#### 5.1.1 Treatment allocation

Patients will be divided into 3 treatment cohortss: Cohort 1, Cohort 2, and Cohort 3. Patients in each cohort were randomized to IBI362: placebo: active comparator = 8:4:2.

#### 5.1.2 Randomization and blinding

This study is a randomized, double-blind trial of IBI362 versus placebo within each dose group. At each dose, each patient will be randomized to receive IBI362, placebo, active control treatment in a ratio of 8:4: 2. If a patient is assigned to receive

IBI362 or placebo, the patient, the investigator, and all personnel involved in the clinical evaluation will be blinded to the treatment from the randomization to database locked, as follows:

Different drug numbers corresponded to random numbers after randomization in the IWRS, and the unblinding information remained unknown to patients and investigators throughout the trial. The randomization table will be kept by a designated person.

The study drug and placebo will be packaged, labeled, administered at the same time, and will have the appearance, taste, and smell exactly the same to hide the real situation of the treatment drug.

If necessary for the safety of the subject, emergency unblinding must be performed using the IWRS.

If a patient is randomized to receive active control, the patient will not be blinded.

Sponsor will not be blinded during this study.

## 5.2 Study Drug

### 5.2.1 Physical and Chemical Characteristics of Drug Substance

|                   |                                                                                                                                                                        |
|-------------------|------------------------------------------------------------------------------------------------------------------------------------------------------------------------|
| Molecular weight: | 4560.32 Dalton                                                                                                                                                         |
| Description:      | White to off-white powder                                                                                                                                              |
| PI:               | 5.2                                                                                                                                                                    |
| Solubility:       | Vehicle: 20 mM Tris buffer pH 8.0 and 150 mM sodium chloride.
Solubility: Not less than 10 mg/mL at 25°C.
Solubility Description: Sparingly or slightly soluble. |

### 5.2.2 Study Drug Strength and Manufacturer

IBI362 is formulated as IBI362 for injection in a strength of 2 mg per vial and consists of 2 mg IBI362 and the inactive ingredients trihydroxymethylaminomethane, mannitol, and sucrose.

The strength of the formulation used in this study is 2 mg/vial; Manufacturer: Supplied by the Sponsor.

Placebo is a lyophilized powder matching IBI362 Manufacturer: Supplied by the Sponsor.

Dulaglutide is supplied as 1.5 mg/0.5 ml single-dose pen manufactured by Vetter Pharma-Fertigung GmbH & Co. KG.

### 5.2.3 Storage

The drug product will be stored in sealed for 2-8°C refrigerator.

